## Abstract

Attention-deficit/hyperactivity disorder (ADHD), a common neurodevelopmental disorder, often persists into adulthood. In Malaysia, the prevalence rate of hyperactivity symptoms is highest among Chinese Malaysians. There are limited evidence-based treatment options targeting the core symptoms of ADHD, as well as executive functioning. In addition, conventional psychotherapeutic approaches for adults with ADHD have been found to be highly labor-intensive. The present study will evaluate the effectiveness of an online mindfulness-based intervention to reduce inattention and hyperactivity–impulsivity and improve executive functioning among Chinese Malaysian college emerging adults with ADHD. Informed by established literature, we will design an 8-week online mindfulness-based intervention (i.e., iMBI). We will conduct a two-arm randomized controlled trial comparing an iMBI plus treatment-as-usual group (*n* = 54) and an enhanced treatment-as-usual control group (*n* = 54). Outcome measures of inattention, hyperactivity–impulsivity, and executive functioning will be collected at baseline, immediately post-intervention, and 1-month post-intervention. The findings of the present study will not only demonstrate the implementation of iMBI as a new treatment modality but also inform practitioners on the effectiveness of iMBI in reducing the burden of adults living with ADHD.

## 1. Introduction

Attention-deficit/hyperactivity disorder (ADHD) is one of the most documented neurodevelopmental disorders in a clinical setting. The *Diagnostic and Statistical Manual of Mental Disorders* (5th ed.; DSM-5) [1] describes ADHD as bidimensional in that it has persistent patterns of inattention and/or hyperactivity–impulsivity leading to significant functional or developmental impairment and executive dysfunctions [2]. ADHD is often regarded as a childhood developmental disorder. However, it may persist into adulthood and have substantial psychiatric comorbidity [3,4,5]. From longitudinal birth cohort studies, it has been estimated that the adult ADHD prevalence rates range from 2% to 6% [6,7,8].

In Malaysia, it was reported that 4.6% of children aged 5 to 15 years old had significant symptoms of hyperactivity [9]. It was also reported that the prevalence rates of the hyperactivity problem were 5.8% among Chinese Malaysian, 4.7% among Malay Malaysian, and 5.3% among Indian Malaysian children [9]. While little epidemiological data are known about adult ADHD in Malaysia, it is reasonable to speculate that the prevalence of such neurodevelopmental disorder among Chinese Malaysian adults would continue to be high, as we inspect the prevalence rate of the hyperactivity problem among Chinese Malaysian children—most individuals’ ADHD symptoms may persist to adulthood.

### 1.1. Emerging Adulthood and ADHD

Emerging adulthood is a distinct developmental phase often taking place from 18 to 25 years old [10]. Issues and challenges that arise during emerging adulthood have received extensive attention from researchers in the past 2 decades. For instance, numerous studies have investigated the demographic status, subjective meaning of adulthood, and identity exploration among emerging adults [10,11,12,13]. Among other issues, psychopathology and mental health problems among emerging adults have been found to be particularly remarkable [14]. Since 2006, late adolescents and emerging adults have had the highest psychiatric morbidity in Malaysia [9,15]. To this end, individuals growing up with ADHD are expected to encounter even more difficulties than their typically developed peers. This notion is supported by past studies indicating that individuals with ADHD had more psychiatric comorbidities [16], greater involvements in risky behaviors [17], higher risk for sexual victimization [18], greater cognitive failure [19], and poorer quality of life [20] as compared with their non-ADHD counterparts.

### 1.2. The Present Study

Based on insights derived from recent empirical research, the present study is devoted to addressing at least five research gaps. These are (1) management of ADHD to improve core symptoms, (2) promotion of non-pharmacological interventions, (3) accessibility of therapy, (4) mindfulness-based intervention as a potential treatment choice, and (5) online intervention as a new treatment modality.

#### 1.2.1. Management of ADHD to Improve Core Symptoms

ADHD is a complex neurodevelopmental disorder contributed to by multiple genetic and environmental risk factors. The neurocognitive deficit theories of ADHD (e.g., executive dysfunction, delay aversion, and dual pathway theories) [21] and neurobiological basis of ADHD [22] have been widely recognized by researchers and clinicians. The theory of impairment of executive functioning proposes a set of neurocognitive strategies leading to the attainment of goals. According to this theory, cognitive deficits such as response inhibition, vigilance, working memory, and planning are most prominent in people with ADHD [23]. However, meta-analytic reviews found that the effect size of existing treatments (e.g., methylphenidate and working memory training) on these executive skills was, at best, small to moderate [24,25]. Such theory suggests a critical need for developing novel and innovative treatments to promote executive functioning. To this end, the present study will focus on inattention, hyperactivity–impulsivity, and executive functioning (in particular, working memory and inhibition) as treatment outcome variables.

#### 1.2.2. Promotion of Non-Pharmacological Interventions

In addition, management of ADHD remains a debatable topic in both scientific and public communities. The National Institute for Health and Care Excellence [26] recommends pharmacological treatments for adults with ADHD who have failed to respond to environmental modifications. Although the efficacy of psychostimulants on ADHD individuals has been well established through numerous high-quality studies [27,28], a number of barriers to pharmacological intervention exist. Individuals with ADHD may have difficulty enjoying the benefits of optimized treatment as a result of nonadherence to ADHD medication [29] and intolerance of adverse effects [30]. In addition, O’Callaghan and Sharma [20] argued that pharmacological therapies may not sufficiently address the psychosocial needs of people with ADHD. Thus, there are ongoing efforts to search for a novel non-pharmacological treatment to maximize desirable clinical outcomes in people with ADHD. The present study will contribute to the limited existing body of knowledge on non-pharmacological interventions by developing and evaluating an online psychotherapeutic program.

#### 1.2.3. Accessibility of Therapy

In Malaysia, non-pharmacological management of ADHD, especially in treatment-resistant cases, is often delivered by clinical psychologists [31]. As reported by the Ministry of Health [32], only 0.03 clinical psychologist (per 1,000,000 population) and 0.01 clinical psychologist (per 1,000,000 population) are available in West and East Malaysia, respectively. The significant scarcity of clinical psychology human resources represents a substantial barrier to service accessibility. Thus, there is an urgent need to improve the accessibility of non-pharmacological therapies for ADHD. Given the advancement of technology, especially in e-mental health, online psychological intervention could be a promising approach to narrow the accessibility gap [33].

#### 1.2.4. Mindfulness-Based Intervention as a Potential Treatment Choice

Mindfulness-based intervention (MBI) is a relatively new psychological intervention modality in modern psychology. The frameworks of this evolving psychotherapy technique date back to about 2500 BC in the Eastern wisdom of spirituality [34]. In the practice of modern medicine, mindfulness’s clinical value was first proven in chronic back pain management in the 1970s [35] and in a wide range of psychiatric disorders in recent years [36,37]. The rationale of employing a mindfulness-based intervention to improve symptoms in emerging adults with ADHD relies on growing evidence of attention-related neuropathway changes resulting from mindfulness practices [38,39,40,41,42,43]. Several empirical studies have indicated that training on mindfulness may also enhance metacognitive processing, where individuals command the skills needed to intentionally self-monitor and regulate their attention and perception [44,45]. Mindfulness training such as mindful breathing could activate neural pathways that are beneficial to attention and executive functions [39]. After a 9-month follow-up, a significant increase in cortical thickness was observed in the right prefrontal cortex extending to the anterior cingulate cortex and in the bilateral occipital regions extending to the inferior temporal cortices among participants receiving mindfulness-based intervention [46]. The said brain regions are known to be associated with attention and executive functioning—the core deficits of people with ADHD. To further support this premise, findings from a recent meta-analysis found that the effectiveness of MBI in alleviating ADHD symptoms, reducing depression, and improving executive functioning was moderate [47]. In this regard, MBI is a good candidate as adjunct therapy for adults with ADHD.

#### 1.2.5. Online Intervention as a New Treatment Modality

The Malaysian Communications and Multimedia Commission reported that 90.1% of Malaysian households have Internet access [48]. Given that a psychological treatment gap does exist in Malaysia, where discrepancies between supply and demand and costs of mental health services are large, online intervention may be a viable alternative. Online interventions have several advantages over conventional face-to-face intervention programs in one important way—they provide self-directive, anonymous, low-cost services and are instantly accessible to communities that otherwise may not have access to mental healthcare services. Evidence from a cross-sectional study also suggests that an Internet-delivered mindfulness program is the first choice of young people [49]. For example, cognitive behavioral therapy (CBT) using an online platform was successfully delivered to people with ADHD [50] and its promising results were reported. Just like online CBT, the effectiveness of an Internet-delivered mindfulness-based intervention to improve mental health was reported in a meta-analytic review of randomized control trials [51].

Taken together, the present study will contribute to the limited existing body of knowledge and current psychiatric management of ADHD by delivering a relatively new treatment modality via a web platform, that is, online mindfulness-based intervention (iMBI). Therefore, the primary objective of the present study is to examine the effectiveness of iMBI in reducing inattention and hyperactivity–impulsivity, and in improving executive functioning among Chinese Malaysian college emerging adults with ADHD.

## 2. Materials and Methods

### 2.1. Study Intervention

A mindfulness-based intervention is typically delivered over 8 weekly structured face-to-face sessions. It aims to cultivate nonjudgmental focused attention on experiences in the present moment [34]. In a group format, an MBI session usually lasts for 2 to 3 h and consists of a short lecture on selected topics, formal and informal in-session practices, and weekly home practices. A search procedure was conducted to identify published research and studies examining the effects of mindfulness on adults with ADHD. Published research and studies were identified by searching eight electronic databases: Scopus, PubMed, ScienceDirect, MEDLINE Complete, PsycArticles, Frontiers, SAGE, and China National Knowledge Infrastructure. Keywords such as attention-deficit/hyperactivity disorder, ADHD, mindfulness, and meditation were included in the search strategies. Four key frameworks concerning the effectiveness of mindfulness-based intervention in reducing inattention and hyperactivity–impulsivity and in improving executive functioning based on insights derived from eight recent empirical research studies were obtained [52,53,54,55,56,57,58,59]. These are (1) psychoeducation on ADHD and mindfulness; (2) mindfulness of physical sensations; (3) mindfulness of cognitive, behavioral, and emotional functioning; and (4) consistent practices of formal and informal mindfulness. We will design an eight-session iMBI in compliance with these four key MBI frameworks.

#### 2.1.1. Online Mindfulness-Based Intervention

Table S1 (see Supplementary Materials) illustrates the proposed outline of the iMBI program. In support of Crane et al. [60], the present program will be developed to meet the specific needs of emerging adults with ADHD. In the present study, iMBI will start with psychoeducation about ADHD and definition of mindfulness (i.e., the first key framework). Participants will engage in a structured discussion session to share about their experiences of living with ADHD. Upon orientation to the program, the participants will be introduced to various topics of mindfulness and ADHD, as well as a wide range of in-session online mindfulness exercises (i.e., the second and third key frameworks). Offline assignments (i.e., the forth key framework) that correspond to a weekly theme will be assigned to the participants at the end of each session. Downloadable audio tracks for offline practices will be provided to the participants. The participants are expected to spend around 15 to 30 min to complete the weekly iMBI session. To examine face and content validities, the proposed program will be reviewed by a group of expert panels, including a family medicine specialist, a psychiatrist, two clinical psychologists, and a developmental psychopathologist. Revision and refinement of the program content will be made based on comments and suggestions from panel discussions. Table 1 displays the mapping of iMBI to outcome variables.

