#### 2.1.2. Enhanced Treatment-as-Usual Control Group

Participants from the enhanced treatment-as-usual (eTAU) control group will receive the usual care that is provided to adults with ADHD across clinical settings in Malaysia, along with a 30 min online psychoeducation webinar on adult ADHD. The participants will be allowed to initiate, maintain, or discontinue a treatment as they wish. We play no role in determining the treatment plan of the participants. However, we will emphasize the importance of seeking treatment as needed from their respective clinicians throughout the trial. The participants will be required to report both pharmacological and non-pharmacological treatments that they have received through an online questionnaire during the trial period. Data from the eTAU control group participants receiving either mindfulness-based intervention or CBT from their treating clinicians during the trial period will be excluded from statistical analysis to avoid data contamination. The participants from the eTAU control group will receive an invitation to participate iMBI upon completion of data collection.

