### 2.10. Study Procedures

Recruitment of participants will take place in different ways. First, participants from the participating university will be randomly recruited. Second, participants will be recruited from the counselling center at the university. Third, participants will be recruited via campus-based online social media sites (e.g., Facebook) and students’ online portal of the participating university. Last but not least, recruitment presentations at the participating university will also be made to recruit participants. We will start to enroll participants in March 2021 by invitation. The trial is expected to begin in May 2021 and end in December 2021.

Interested individuals will receive a study information sheet and will be invited to a screening session to determine their eligibility. Written informed consent will be obtained from all participants. Eligibility of participants will be assessed using screening and diagnostic measures 2 weeks before the program starts. Data collection will be conducted at a designated laboratory. Participants will be required to complete all study measures. Outcome measures, including attention, hyperactivity, and executive functioning (working memory and inhibition), will be collected at baseline, immediate post-intervention, and 1-month follow-up. Figure 1 presents the Consolidated Standards of Reporting Trials (CONSORT) diagram of the present study.

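### The contamination rule covers only mindfulness or CBT given to controls by treating clinicians, and it acts by dropping them after randomisation; exposure from other sources falls outside it

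*Protocol article*

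**What the plan says.** Section 2.1.2 sets the only contamination rule. Data from controls "receiving either mindfulness-based intervention or CBT from their treating clinicians during the trial period will be excluded from statistical analysis to avoid data contamination". No other source of exposure is named, and no matching rule is given for the iMBI arm. The same section provides for reporting: "The participants will be required to report both pharmacological and non-pharmacological treatments that they have received through an online questionnaire during the trial period".

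Section 2.1.1 gives the iMBI arm material for practice outside the sessions: "Downloadable audio tracks for offline practices will be provided to the participants". It identifies the offline assignments with the fourth of the programme's four key frameworks, which Section 2.1 describes as consistent formal and informal practice.

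Section 2.3 randomises individuals and tells them only that they will receive an online healthcare programme. Under Section 2.10, "participants from the participating university will be randomly recruited", and "participants will be recruited via campus-based online social media sites (e.g., Facebook) and students’ online portal of the participating university". Section 2.4 speaks more broadly of universities or colleges in Malaysia. Section 2.6 excludes people who had mindfulness training in the previous two years and does not restrict who gave it.

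**The concern.** Exposure to mindfulness is defined broadly before randomisation and narrowly after it, when it can affect the treatment comparison. A control who follows a mindfulness app, or practises with tracks passed on by a fellow student, has received nothing from a clinician and so falls outside the rule. The questionnaire asks about treatments received, and a control who does not know what the other arm contains may not think of an app or an audio file as a treatment.

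Two things are at stake. Exposed controls who benefit shrink the observed difference, and a null result could then mean either that iMBI does not work or that controls practised too. In addition, the remedy chosen for the exposure that is covered removes randomised participants from one arm only, on the basis of what they did after allocation. That gives up the balance that randomisation provides, and the direction of the resulting bias depends on which controls seek such treatment.

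**Working it through.** **Scope of the rule, read against the rest of the article**

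- Source: at entry, mindfulness training from anyone (Section 2.6); during the trial, only from treating clinicians (Section 2.1.2).
- Arm: the exclusion applies to controls only.
- Setting: individual randomisation (Section 2.3) places both arms within the same institution or institutions, whether Section 2.10 (one participating university) or Section 2.4 (universities or colleges) is followed.
- Sample size: Section 2.5 allows for 20% attrition and states no allowance for contamination.

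**The plan's own figure**

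Section 2.5 asks for 45 per arm at 80% power and α = 0.05, but gives only ranges of d: 0.33 to 3.14, 0.24 to 1.32 and 1.08 to 2.16. The figure of 45 therefore cannot be reproduced. Solving backwards with a two-sided two-sample t-test (the article does not state sidedness), 45 per arm gives 80% power at d = 0.597. I use d = 0.60 as a working value; it is an assumption.

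**Illustration of dilution**

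Let c be the share of the effect lost. If a proportion p of controls is exposed and each gains a fraction b of the full effect, then c = p × b.

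- Observed effect: d × (1 − c).
- Power: noncentral t with 2 × 45 − 2 = 88 degrees of freedom, noncentrality d × (1 − c) × √(45/2), critical value 1.987.

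| c | Observed d | Noncentrality | Power |
|---|---|---|---|
| 0 | 0.60 | 2.846 | 80.4% |
| 5% | 0.60 × 0.95 = 0.57 | 2.704 | 76.2% |
| 10% | 0.60 × 0.90 = 0.54 | 2.561 | 71.7% |
| 20% | 0.60 × 0.80 = 0.48 | 2.277 | 61.5% |

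With b = 1, c equals the proportion of controls exposed, which is the upper bound. If audio alone gave a quarter of the benefit (b = 0.25, also an assumption):

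- p = 5%: c = 1.25%, d = 0.5925, power 79.4%.
- p = 10%: c = 2.5%, d = 0.585, power 78.4%.
- p = 20%: c = 5%, d = 0.57, power 76.2%.

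These are unadjusted t-test figures. Section 2.11 plans a MANCOVA with baseline covariates, so they show the direction and rough scale of the loss and do not give the trial's actual power.

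**The case against.** A reader might infer that the practice audio is circulating on a campus shared by both arms and that contamination would go wholly unseen. The article does not support this. It says only that tracks are provided to participants. The reporting sentence in Section 2.1.2 is not limited to clinicians, so the questionnaire could capture some informal practice, and its wording is not shown. Log-in limits or a request not to share may be in the full protocol, so their absence from the article is no error. Section 2.4 also allows for more than one institution.

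Nor can one infer that peers are a likelier route than clinicians. The scarcity figures in Section 1.2.3 count clinical psychologists, and treating clinicians is a wider group.

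Another tempting reading is that early controls would hold the programme while others are still in follow-up. The sentence is "The participants from the eTAU control group will receive an invitation to participate iMBI upon completion of data collection", which most naturally means the end of data collection for the whole trial.

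It can also be argued that self-chosen apps belong to usual care, since controls may start any treatment they wish. That is a fair choice of comparison, but Section 2.1.2 already treats clinician-delivered mindfulness as contamination. If the same practice from another source is to count as usual care, the distinction needs a reason.

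Finally, asking controls about mindfulness at week 8 could reveal the other arm's content before their week-12 outcomes. That objection stands, and it determines when the question should be asked.

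What remains is that the stated rule is narrow, applies to one arm, and works by exclusion after randomisation.

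**Conclusion.** The point holds as a weakness in how the rule is fixed. Contamination is defined by who delivered the treatment, when what matters is exposure, and the response is to drop controls when they could be kept and their exposure examined. Mindfulness practice from other sources is a plausible route that the rule does not reach, the questionnaire may not record it, and it would bias the comparison towards no effect.

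The size cannot be derived from the documents, because no contamination rate is given. Under the assumptions above, power falls from about 80% to between 76.2% and 61.5% when 5% to 20% of the effect is lost, and to between 79.4% and 76.2% when the same proportions of controls gain only a quarter of the benefit. The ambiguity of a null result does not depend on any particular rate. The change is a worthwhile, inexpensive improvement; the article does not show that the trial is contaminated.

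**What to change.** Replace the clinician-only exclusion in Section 2.1.2 with three provisions:

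1. Ask both arms once, after the week-12 outcome scales are complete, whether they practised mindfulness or received CBT from any source during weeks 0 to 12, and how much. Word the item neutrally and do not name trial audio, so that the blinding in Section 2.3 is kept and no outcome is cued.
2. Keep all randomised participants in the main comparison, whatever exposure they report.
3. Report exposure by arm and use it in a sensitivity analysis.

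The cost is one or two questionnaire items, a few sentences of protocol text and a 12-week recall period, which will make reported amounts of practice imprecise.

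Two clarifications are optional: whether access to the audio is limited to each participant's log-in, and that the invitation to controls follows the last participant's week-12 assessment. Restricting access would make offline practice slightly less convenient.
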